### **4.1.3 Others**

#### **4.1.3.1 Baseline information**

Prior to entry into the study, details of the study objectives and contents will be explained to, and written informed consent will be obtained from the subjects. In the order of written informed consent, screening number will be assigned to these subjects, and their baseline information will be collected. Information to be documented includes status of written informed consent and date

of consent, gender, date of birth, age, and drinking history.

Drinking history will be assessed based on the volume of alcohol consumed per week within the last 1 month (30 days). Alcohol abuse is defined as alcohol consumption exceeding 21 units\* per week.

\* 1 unit: alcohol 8~12 g = one glass of soju

- One bottle of 21% soju = 6.7 glasses of soju, 21 units = approximately 3 bottles of soju
- One 500 cc glass of beer (4%) = 1.8 glasses of soju, 21 units = approximately 11 glasses of beer
- One big glass of wine = 2 glasses of soju, one small glass of wine = 1 glass of soju, 21 units = approximately 10.5 ~ 21 glasses

#### **4.1.3.2 Medical history taking**

Details of medical history will be collected via interviews and past medical records and documented. For past medical history including surgical history and allergies within 1 month prior to screening as well as current medical history, time of onset (year and/or month of onset) and status of continuation at the time of screening will be recorded. The following medical history will be collected regardless of time of onset: history of SARS-CoV, MERS-CoV and/or SARS-CoV-2 infection, history of hypersensitivities to vaccinations such as Guillain-Barré syndrome, history of allergy or hypersensitivity reactions to any of the components of the IP, history of SAEs with and/or allergy to antibiotics and/or non-steroidal anti-inflammatory drugs, and history of thrombocytopenia or other coagulation disorders.

#### **4.1.3.3 Medication history taking**

Medication history within 1 month prior to screening (prior drugs and concomitant drugs) and details of medication (dosage and administration, duration of treatment, etc.) will be collected. As part of the exclusion criteria, history of vaccination against SARS-CoV, MERS-CoV, or SARS-CoV-2 will be collected regardless of time of vaccination. As for history of treatment with other IPs and/or other investigational devices, antipsychotics, and opioid analgesic dependence, information within 6 months will be collected. As for history of systemic steroids, immunosuppressants/immune modifying drugs, anticancer therapy, and immunoglobulin or other blood transfusions, information within 3 months will be collected.

Any change in medication history from screening will be checked; details of any change in concomitant medication must be recorded in the source document.

#### **4.1.3.4 Height and weight measuring**

Height and body weight will be measured at screening. Before measuring body weight, the subject will be instructed to take off outer clothing and shoes and to empty pockets.

#### **4.1.3.5 Chest X-ray and electrocardiogram**

At the screening visit, posterior-anterior X-ray and electrocardiogram (ECG) will be performed. During the screening period, one re-test may be performed at the discretion of the investigator.

#### **4.1.3.6 COVID-19 diagnostic test and antibody test**

At the screening visit and Visit 2, subjects will be tested for COVID-19 for the inclusion/exclusion criteria checking. Using upper respiratory tract sampling (oropharyngeal/ nasopharyngeal swab) and lower respiratory tract sampling (an additional sputum test will be performed in the presence of symptoms such as cough and sputum), reverse transcription-polymerase chain reaction (RT-PCR) diagnostic test and COVID-19 antibody test (positivity to IgM and IgG; 20 µL of blood) will be performed to determine past and/or current COVID-19 infection. During screening, antibody test will be performed as clinical laboratory test and at Visit 2, the test may be performed by the institution or the COVID-19 diagnostic kit provided by the sponsor.

Subjects who have the following symptoms of COVID-19 infection after randomization should follow the guideline on COVID-19 by ‘Central Disease Control Headquarters · Central Disaster Management. Headquarters’ and inform the symptoms to the investigator. As much as possible, the subjects should be instructed to visit the institution and have medical treatment and diagnosis.

- $\geq 37.5^{\circ}\text{C}$  fever or chills, fatigue, myalgia or body aching, headache, sore throat, anosmia and ageusia, nasal obstruction or nasal discharge, nausea or vomiting, diarrhea, cough, respiratory distress or respiratory disturbance

#### **4.1.3.7 Pregnancy test**

At the screening visit, prior to the 2nd dose of the IP (Visit 5), at the end of main study visit (Visit 9), and at the end of follow-up visit (Visit 11), all women of childbearing potential, except for surgically sterile women and post-menopausal women (including surgical menopause), will be tested for pregnancy by urine or serum hCG (approximately 5 mL of blood) testing. Women of childbearing potential are defined as those who had menarche and are not surgically sterile (hysterectomy, bilateral tubal ligation, or bilateral ovariectomy) or postmenopausal. Menopause is defined as having no menses for  $\geq 12$  months from the final menstrual period without an alternative cause.

#### **4.1.3.8 Re-screening**

One re-screening can be performed on those who fail in screening. For re-screening, a new written informed consent will be obtained, a new screening number will be granted, and all of the Visit 1 procedures will be carried out.

### **4.2 Procedures by visit**

The same procedures will be applied to Part A and Part B. Subjects participating in this study must comply with 「Guidelines for the prevention of COVID-19」 presented by Korea Centers for Disease Control & Prevention.

#### **4.2.1 Visit 1 (screening, Day -7 ~ Day -1)**

Once prior-consenting procedures are completed and written informed consent is obtained, the subject will be granted a screening number and assessed as follows. Written informed consent can be obtained prior to Visit 1; if all tests are not done at Visit 1, the subject may have another visit for the tests before the randomization at Visit 2.

- Demographic information and medical history (past medical history including surgical history and current medical history) as well as prior and concomitant medications will be taken/documented.

- Vital signs will be measured.
- Physical examination will be conducted.
- Height and weight will be measured.
- Chest X-ray and ECG will be performed.
- Clinical laboratory tests (hematology, blood chemistry, urinalysis, blood coagulation, virus) will be performed.
- Pregnancy test will be performed for women of childbearing potential.
- RT-PCR diagnostic test and antibody test for COVID-19 will be performed.
- The inclusion/exclusion criteria will be checked.
- The next visit day will be scheduled.

#### **4.2.2 Visit 2 (1st dose of the IP, Day 0)**

This visit will take place within 7 days after the initial visit. Procedures to be carried out during this visit are as follows. For those who meet all of the inclusion/exclusion criteria at screening, Visits 1 and 2 can simultaneously be conducted with overlapping procedures done only once. In this case, baseline test results will be replaced with screening test results for the purpose of analysis.

- Any change from the last visit in medical history and prior/concomitant medications will be checked.
- Vital signs will be measured.
- Physical examination will be conducted.
- RT-PCR diagnostic test and antibody test for COVID-19 will be performed.
- Based on overall results of all tests and evaluations performed up to this point including clinical laboratory tests, a final decision will be made on the eligibility of the subject according to the inclusion/exclusion criteria.
- Subjects will be randomized in the order of enrollment and given a randomization number.
- Prior to dosing, a blood sample will be collected for immunogenicity testing and the time of blood sampling will be recorded.
- The IP will be administered and the date and time of administration will be recorded
- The subject will be monitored for 30 minutes post-dose for immediate AEs (anaphylaxis associated).
- The subject will be provided with a ruler and a digital thermometer (for tympanic temperature). The subject will also be given a subject diary and instructions on how to

complete the diary in order to collect and monitor solicited and unsolicited AEs.

- The next visit day will be scheduled.

#### **4.2.3 Visit 3 (telephone visit, 2 ~ 5 days after the 1st dose)**

This visit will take place by a telephone call made by a trained sub-investigator to the subject between 2 days and 5 days after the 1st dose of the IP.

- Any AEs and any change in concomitant medications since the last visit will be checked.
- The subject will be instructed to record any solicited and unsolicited AEs.
- The next visit day will be scheduled.

#### **4.2.4 Visit 4 (interim visit for the main study, 7 + 3 days after the 1st dose)**

This visit will take place on Day 7 after the 1st dose of the IP. Procedures to be carried out during this visit are as follows.

- Any change from the last visit in concomitant medications will be checked.
- The subject diary will be retrieved for status and details of AEs.
- Vital signs will be measured.
- Physical examination will be conducted.
- Clinical laboratory tests (hematology, blood chemistry, urinalysis) will be performed.
- The subject will be given a subject diary and instructions on how to complete the diary.
- The next visit day will be scheduled.

#### **4.2.5 Visit 5 (2nd dose of the IP, 21 + 5 days after the 1st dose)**

This visit will take place on Day 21 after the 1st dose of the IP. Procedures to be carried out during this visit are as follows.

- Any change from the last visit in prior and concomitant medications will be checked.
- The subject diary will be retrieved for status and details of AEs.
- Vital signs will be measured.
- Physical examination will be conducted.
- Pregnancy test will be performed for women of childbearing potential.

- Prior to dosing, a blood sample will be collected for immunogenicity testing and the time of blood sampling will be recorded.
- Contraindications for the 2nd dose of the IP will be checked. If the subject meet the criteria of contraindications for the 2nd dose of the IP, subjects will be treated in accordance with section 5.4 'Criteria for subject discontinuation and withdrawal' and proceeded with the procedure of Visit 9.
- The IP will be administered and the date and time of administration will be recorded.
- The subject will be monitored for 30 minutes post-dose for immediate AEs (anaphylaxis associated).
- The subject will be given a subject diary and instructions on how to complete the diary.
- The next visit day will be scheduled.

If the following symptoms are observed in a subject planned to have the 2nd dose, dosing can be rescheduled within the visit window.

- $\geq 37.5^{\circ}\text{C}$  fever
- Acute infectious disease requiring delayed IP dosing in the opinion of the investigator

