- 11) If possible, subjects who are withdrawn from the study will visit the institution for required procedures. Those who are withdrawn prior to Visit 9 (end of main study visit) will perform Visit 9 procedures. Those who are withdrawn after Visit 9 will perform Visit 11 procedures (end of follow-up visit) except for blood sampling for immunogenicity testing. If consent is obtained from the subject, telephone visits will be conducted by a trained sub-investigator who will call the subject at the time points of Visit 10 (Week 26 after the 2nd dose of the IP) and Visit 11 (Week 52 after the 2nd dose of the IP) for serious ADRs and AESIs. Subject who has not performed administration of 2nd dose investigational product will conduct Visit 10 and Visit 11 on the basis of scheduled date of 2nd dose administration.
- 12) Concomitant drugs administered for SAEs and AESIs will be collected.
- 13) Status of SAEs and AESIs will be checked. In the event of an AESI, additional tests may be conducted as necessary at the discretion of the investigator, and if necessary, the DSMB may meet to review the case for status of ADR and enhanced disease.

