### **5.4 Criteria for subject discontinuation and withdrawal**

Those who are randomized but cannot participate in the study for the entire period for any reason will be classified as dropouts. Subjects may choose to discontinue the study at any time for any reason by requesting withdrawal. Or subjects may also be discontinued at any time for safety, behavioral, or administrative reasons at the discretion of the investigator or the sponsor. The investigator should ask about reasons for withdrawal and ask the subject to return for the last visit. If applicable, the investigator should make every effort to follow up on unresolved AEs.

For the following reasons, subjects may ask for withdrawal or may be discontinued or withdrawn

upon discussion with the investigator and the sponsor. In this case, the reasons and actions taken for the discontinuation and withdrawal should be recorded on the relevant document as well as on the CRF:

- ① The subject or his/her representative withdraws informed consent.
- ② Violation of the inclusion/exclusion criteria is identified during the course of the study.
- ③ The subject corresponds to exclusion criteria for 2nd dose.
- ④ The subject or his/her representative wants to discontinue the study due to unsatisfactory therapeutic effects during the study period.
- ⑤ The subject does not comply with instructions of the principal investigator or the sub-investigator.
- ⑥ Lost to follow-up.
- ⑦ The subject becomes pregnant during the study period.
- ⑧ Study participation is inappropriate for other reasons based on the judgment of the sponsor or the investigator

If possible, subjects who are withdrawn after Visit 2 and before Visit 9 (end of main study visit) will return to the institution for Visit 9 procedures. If possible, those who are withdrawn after Visit 9 will return to the institution for Visit 11 (end of follow-up visit) procedures except for blood sampling for immunogenicity testing. For safety follow-ups for dropouts, if consent is obtained from the subject, telephone visits will be conducted by a trained sub-investigator who will call the subject at the time points of Visit 10 (Week 26 after the 2nd dose of the IP) and Visit 11 (Week 52 after the 2nd dose of the IP) for SADRs and AESIs.

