## 5.5 Criteria for study suspension

During the study period, subjects will be monitored for the following ADRs that serve as criteria for study suspension. In the event of ADRs that are the criteria for study suspension, additional enrollment and treatment will be stopped at this time, and the DSMB will meet to decide study continuation.

- 1) Part A study: Grade  $\geq 3$  ADRs occurring within 7 days after the 1st dose in the first 5 subjects
- 2) Part A and Part B studies:
  - ① Grade  $\geq 3$  ADRs occurring within 3 days (Day 0 ~ Day 2) from the respective dosing day and lasting for  $> 1$  day despite active intervention for resolution in  $\geq 15\%$  of all

subjects planned to be enrolled to each study group (Part A:  $\geq 8/50$  subjects, Part B:  $\geq 35/230$  subjects)

- ② SADRs or Grade  $\geq 4$  ADRs occurring within 28 days after the respective dose of the IP

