## 7.2 Endpoints

### 7.2.1 Safety endpoints

- AEs
  - ① Immediate AEs occurring within 30 minutes after each IP dosing
  - ② Solicited local and systemic AEs occurring for 7 days (Day 0~ Day 6) after each IP dosing
    - ✓ Local AEs : pain, tenderness, erythema/redness, induration/swelling, itchiness
    - ✓ Systemic AEs : fever, fatigue/malaise, chills/rigors, headache, myalgia, joint pain, diarrhea, vomiting, abdominal pain, mucocutaneous reaction/rash, cough, acute bronchospasm, respiratory distress
  - ③ Unsolicited AEs occurring within 28 days after the last IP dosing
  - ④ SAEs occurring within 52 weeks after the last IP dosing
  - ⑤ AESIs occurring within 52 weeks after the last IP dosing
- Clinical laboratory tests (hematology/blood chemistry, urinalysis)
- Vital signs
- Physical examination

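### A subject refused dose 2 gets the end-of-main-study procedures at Visit 5, so collection of new unsolicited adverse events stops 2 to 7 days short of the protocol's own 28-day window

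*Protocol*

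**What the plan says.** **Rule at Visit 5.** Visit 5 is timed at "21 + 5 days after the 1 st dose". If a contraindication to dose 2 is found there, section 4.2.5 refers the subject to section 5.4 "and proceeded with the procedure of Visit 9". Section 5.3 lists the contraindications. They include anaphylaxis or generalized hypersensitivity after dose 1 and serious events related to the product, and also COVID-19 positivity, need for a prohibited drug, coagulation disorders, pregnancy and investigator judgement.

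**Status of the subject.** Section 5.4 states: "Those who are randomized but cannot participate in the study for the entire period for any reason will be classified as dropouts". Its list of withdrawal reasons includes "The subject corresponds to exclusion criteria for 2 nd dose". It also says: "If applicable, the investigator should make every effort to follow up on unresolved AEs".

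**What Visit 9 does.** Under section 4.2.9 the diary is retrieved and none is handed out. For those who leave before Visit 9, later scheduled contact is by telephone at the Visit 10 and 11 time points, if the subject consents, and covers serious adverse drug reactions and events of special interest. Section 5.4 and footnote 11 of the Schedule of Assessments say the same.

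**The windows that need 28 days.** The endpoint in section 7.2.1 is "Unsolicited AEs occurring within 28 days after the last IP dosing", and section 7.3.4.1 analyses the same window. Footnote 10 runs the diary for unsolicited events to Day 28 after each dose.

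**The one place that re-times visits for a subject without dose 2.** Footnote 11 says such a subject "will conduct Visit 10 and Visit 11 on the basis of scheduled date of" the second dose. It does not mention Visit 9.

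**The concern.** The endpoint is counted from the last dose received, but the end of collection is tied to dose 2. Section 8.2 ends general event collection at Day 28 after dose 2 and gives no end for a subject who never has it. Section 4.2.5 then brings the closing visit forward to a day before the endpoint window has run out. The duty in section 5.4 to follow unresolved events does not reach events that start after that visit.

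Safety is the primary objective of Part A, and the monitoring board decides on Part B from Part A safety data. The Safety Set (section 7.3.1) keeps every dosed subject in the denominator, so a one-dose subject counts in full but is observed for less time. Some of the reasons for refusing dose 2 are themselves severe dose 1 reactions, so for those subjects the shortening is related to the safety outcome.

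**Working it through.** This is date arithmetic on the visit windows, with dose 1 on Day 0.

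**1. Reproduce the protocol's own figure.** Footnote 10 places Day 28 after dose 1 at Visit 7.
- Earliest Visit 7 = 21 + 7 = Day 28.
- Latest Visit 7 = (21 + 5) + (7 + 3) = Day 36.

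So a subject who has both doses keeps a diary for at least 28 days after dose 1, as stated. Visit 9 for that subject falls between 21 + 28 = Day 49 and (21 + 5) + (28 + 7) = Day 61.

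**2. Apply the rule to a subject refused dose 2 at Visit 5.**
- The last dose is dose 1, so the section 7.2.1 window ends on Day 28.
- The Visit 9 procedures, done as part of Visit 5, fall on Day 21 to Day 26.
- Shortfall = 28 − day of the closing visit.
- At Day 21: 28 − 21 = 7 days, and 7/28 = 25%.
- At Day 26: 28 − 26 = 2 days, and 2/28 = 7%.

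**3. What is lost in those days.**
- Solicited events after dose 1 (Day 0 to 6) are complete: that diary is retrieved at Visit 4.
- Events already open at the visit are still followed (sections 5.4 and 8.2).
- Serious events and events of special interest are collected to Visit 11, and subjects are asked to telephone any Grade 3 or higher event over the same period (section 8.2). Section 8.4 requires all serious events to Visit 11 to be reported.
- What remains exposed is mainly new, non-serious Grade 1 or 2 unsolicited events with onset after the closing visit.

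**4. Weight of one subject.** A Part A dose group has 15 vaccinees. One missed event of a term not otherwise recorded for that subject changes that term's incidence by 1/15 = 6.7 percentage points. The proportion with any event does not change for a subject who already has one on record.

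**5. Two related inconsistencies.**
- Sections 8.2 and 8.4 collect all serious events to Visit 11. For those who drop out before Visit 9, section 4.2.9, section 5.4 and footnote 11 limit the calls to serious adverse drug reactions and events of special interest. For those withdrawn after Visit 9, section 4.2.11 asks about all serious events.
- Footnote 11 has a subject without dose 2 conduct Visits 10 and 11, while section 5.4 gives a dropout only consent-based calls.

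**The case against.** The strongest reply is that the gap is small and falls on the least important events. That stands: at Visit 5 it is 2 to 7 days, and the more serious events have the routes listed above.

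It can also be said that section 5.4 speaks of withdrawn subjects returning for the Visit 9 procedures, which could mean a later day. But section 4.2.5 puts the instruction inside the Visit 5 list, and Visit 9 is defined only from dose 2, so a site reading it that way still has no date to work to.

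Footnote 11 and section 5.4 can be read together: the footnote contains the same telephone sentence, and its last sentence may only fix the date basis for Weeks 26 and 52. That is fair. What remains is a lack of clarity about the mode of contact.

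Three stronger readings are tempting, and the document does not support them.
- *Near-total loss after an immediate reaction.* A reader might infer that a subject with anaphylaxis on Day 0 leaves within days and loses nearly the whole window, including the solicited diary. Nothing orders this. Section 5.4 says subjects may be withdrawn after discussion and fixes no day. If exit happened at Visit 4 (an assumption), the loss would be 28 − 10 = 18 to 28 − 7 = 21 days, but that is not the stated rule.
- *Under-counting for the suspension rule.* Section 5.5 counts serious or Grade 4 or higher "ADRs occurring within 28 days after the respective dose of the IP". These events have the section 8.2 and 8.4 reporting routes whatever the date of Visit 9. The weakness is only that capture leans on the subject calling in, using a severity scale in a diary already handed back.
- *Bias confined to the vaccine arms.* Several contraindications can arise equally on placebo, so a selective effect is plausible for reaction-driven refusals but not shown overall.

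**Conclusion.** The point holds in limited form. Followed as written, section 4.2.5 closes collection of new unsolicited events 2 to 7 days (7% to 25%) before the end of the window in sections 7.2.1 and 7.3.4.1 and the diary period in footnote 10, and no other section restores those days. This assumes that the Visit 9 procedures are done on the Visit 5 day, and that Visit 5 falls within its window. An exit before Visit 5 would lose more, but by an amount the protocol does not fix.

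The shortening depends partly on the dose 1 outcome, so it should not be treated as random loss. The number of subjects affected is not given and is probably small. It is worth correcting because the protocol contradicts its own safety window in subjects who stay in the Safety Set, and because correction is cheap.

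**What to change.** Reconcile sections 4.2.5, 5.4 and 8.2 and footnote 11 as follows.
- For a subject who receives only dose 1 and does not withdraw consent, the diary and adverse event collection continue to 28 (+7) days after the last dose received. The Visit 9 procedures, or at least a telephone event check and return of the diary, take place then.
- State in section 8.2 when event collection ends for a one-dose subject.
- State once, consistently, whether Visits 10 and 11 are site visits or calls for these subjects, and whether all serious events or only serious adverse drug reactions are collected.

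This changes data collection only. The dosing and contraindication rules stay as they are, as do the withdrawal rules for pregnancy (section 8.6 and footnote 6) and for unblinding (section 6.5). Safety follow-up can continue after withdrawal.

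The cost is amendment wording and one later visit or call for the few subjects refused dose 2. No new type of assessment is needed.
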